## 8.3 ADVERSE EVENTS AND SERIOUS ADVERSE EVENTS

### 8.3.1 DEFINITION OF ADVERSE EVENTS (AE)

As per the Health Canada Food and Drug Act, an Adverse Event (AE) is defined as: “Any adverse occurrence in the health of a clinical trial subject who is administered a drug that may or may not be caused by the administration of the drug, and includes adverse drug reaction.”

An Adverse Drug Reaction (ADR) is defined as “Any noxious and unintended response to a drug that is caused by the administration of any dose of the drug”.

### 8.3.2 DEFINITION OF SERIOUS ADVERSE EVENTS (SAE)

Any adverse occurrence of a clinical trial subject who is administered a drug or placebo that may or may not be caused by the administration of the drug or placebo that results in:

- in-patient hospitalization
- prolongation of existing hospitalization
- that causes a congenital malformation or birth defect
- that results in a persistent or significant disability or incapacity
- is life-threatening
- results in death

An adverse event (AE) or suspected adverse reaction is considered "serious" if, in the view of either the Site Investigator or Sponsor/Principal investigator, it results in any of the following outcomes: death, a life-threatening adverse event, inpatient hospitalization or prolongation of existing hospitalization, a persistent or significant incapacity or substantial disruption of the ability to conduct normal life functions, or a congenital anomaly/birth defect.

Important medical events that may not result in death, be life-threatening, or require hospitalization may be considered serious when, based upon appropriate medical judgment, they may jeopardize the participant and may require medical or surgical intervention to prevent one of the outcomes listed in this definition.

Due to the nature of the illness being studied, some participants may be hospitalized for IV rehydration or ongoing oral rehydration, vomiting, fever, diarrhea, abdominal pain, and/or dehydration. Hospitalization for these reasons will not be reported as a SAE because it is an expected outcome and treatment for this illness.

### 8.3.3 CLASSIFICATION OF AN ADVERSE EVENT

All adverse events will be classified according to **MedDRA (Medical Dictionary for Regulatory Activities)** – a multilingual standardized international medical terminology dictionary used for “regulatory communication and evaluation of data pertaining to medicinal products for human use.”

#### 8.3.3.1 SEVERITY OF EVENT

Adverse Events will be assessed for severity by the site investigator using the following definitions of severity:

- **Mild:** Events require minimal or no treatment and do not interfere with the participant’s daily activities.
- **Moderate:** Events result in a low level of inconvenience or concern with the therapeutic measures. Moderate events may cause some interference with functioning.
- **Severe:** Events interrupt a participant’s usual daily activity and may require systemic drug therapy or other treatment. Severe events are usually potentially life-threatening or incapacitating. *Note:* The term “severe” does not necessarily equate to “serious”.

---

### 8.3.3.2 RELATIONSHIP TO STUDY INTERVENTION

All adverse events (AEs) must have their relationship to study intervention assessed by the site investigator/clinician who examines and evaluates the participant based on temporal relationship and his/her clinical judgment. The degree of certainty about causality will be graded using the categories below. In a clinical trial, the study product must always be suspect.

- **Definitely Related** – There is clear evidence to suggest a causal relationship, and other possible contributing factors can be ruled out. The clinical event, including an abnormal laboratory test result, occurs in a plausible time relationship to study intervention administration and cannot be explained by concurrent disease or other drugs or chemicals. The response to withdrawal of the study intervention (dechallenge) should be clinically plausible. The event must be pharmacologically or phenomenologically definitive, with the use of a satisfactory rechallenge procedure if necessary.
- **Probably Related** – There is evidence to suggest a causal relationship, and the influence of other factors is unlikely. The clinical event, including an abnormal laboratory test result, occurs within a reasonable time after administration of the study intervention, is unlikely to be attributed to concurrent disease or other drugs or chemicals, and follows a clinically reasonable response on withdrawal (dechallenge). Rechallenge information is not required to fulfill this definition.
- **Potentially Related** – There is some evidence to suggest a causal relationship (e.g., the event occurred within a reasonable time after administration of the trial medication). However, other factors may have contributed to the event (e.g., the participant’s clinical condition, other concomitant events). Although an AE may rate only as “possibly related” soon after discovery, it can be flagged as requiring more information and later be upgraded to “probably related” or “definitely related”, as appropriate.
- **Unlikely to be related** – A clinical event, including an abnormal laboratory test result, whose temporal relationship to study intervention administration makes a causal relationship improbable (e.g., the event did not occur within a reasonable time after administration of the study intervention) and in which other drugs or chemicals or underlying disease provides plausible explanations (e.g., the participant’s clinical condition, other concomitant treatments).
- **Not Related** – The AE is completely independent of study intervention administration, and evidence exists that the event is definitely related to another etiology. There must be an alternative, definitive etiology documented by the clinician.

---

### 8.3.3.3 EXPECTEDNESS

The site investigator or co-investigator will be responsible for determining whether an adverse event (AE) is expected or unexpected. An AE will be considered unexpected if the nature, severity, or frequency of the event is not consistent with the risk information previously described for the study intervention.

The most common adverse events reported related to the use of ondansetron oral solution are: headache, constipation, and sensation of flushing. These adverse events will be considered expected.

---

#### 8.3.4 TIME PERIOD AND FREQUENCY FOR EVENT ASSESSMENT AND FOLLOW-UP

The occurrence of an adverse event (AE) or serious adverse event (SAE) may come to the attention of study personnel during the follow-up questionnaires performed with caregivers or if a study participant presents for medical care to the enrolling ED, or upon review of data by a study monitor.

All AEs including local and systemic reactions not meeting the criteria for SAEs will be captured on the appropriate case report form (CRF). Information to be collected includes an event description, date and time of onset, clinician's assessment of severity, relationship to study product (assessed only by those with the training and authority to make a diagnosis), and date and time of resolution/stabilization of the event.

Any medical condition that is present at the time the participant is screened will be considered as baseline and not reported as an AE. However, if the study participant's condition deteriorates at any time during the study, it will be recorded as an AE.

Changes in the severity of an AE will be documented to allow an assessment of the duration of the event at each level of severity to be performed. AEs characterized as intermittent require documentation of onset and duration of each episode.

Study staff and the site or co-investigator will record all reportable events with start dates occurring any time after informed consent is obtained until 7 (for non-serious AEs) or 15 days (for SAEs) after the last day of study participation.

During each follow up contact made, the investigator/study staff will inquire about the occurrence of AE/SAEs since the last contact (via telephone or email). Events will be followed for outcome information until resolution or stabilization.

As listed in section 1.3 Schedule of Activities, Adverse Events will be assessed via telephone or email contact with the caregiver 24, 48, and 168 hours after enrollment in the study. Possible Adverse Events will be assessed using open-ended feedback questions on the follow-up questionnaires. Trained research study staff will review the response provided by the caregiver and will follow up by telephone as soon as possible. Details regarding the event will be obtained via telephone and contact will be made daily, or weekly, as required to obtain the resolution/stabilization details.

---

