## 1.3 SCHEDULE OF ACTIVITIES (SOA)

Below is a list of study activities identified by study time point. The study period will last 168 hours (7 days) from the Screening/Enrollment Visit to the Final Evaluation (*a 14 day and 30 day completion window is provided for follow-up questionnaires and collection of chart review data respectively*).

|                                                                     | Presenting ED Visit
Screening | Presenting ED Visit
Enrollment/
Baseline Evaluation | Hour 8
Post Ondansetron
Administration – ED | Hour 24*
Evaluation #1 | Hour 48*
Evaluation #2 | Hour 168 (Day 7)* +
14 days
Evaluation #3 (Final) | Hour 168 (Day 7) +
30 days
Chart Review |
|---------------------------------------------------------------------|----------------------------------|-----------------------------------------------------------|---------------------------------------------------|---------------------------|---------------------------|---------------------------------------------------------|-----------------------------------------------|
| Procedures                                                   |                                  |                                                           |                                                   |                           |                           |                                                         |                                               |
| Assessment of eligibility
Inclusion/Exclusion             | X                                |                                                           |                                                   |                           |                           |                                                         |                                               |
| Informed consent
Time 0                                   | X                                | X                                                         |                                                   |                           |                           |                                                         |                                               |

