**Return visits for unscheduled care** to a health care provider related to vomiting, diarrhea, dehydration, fever, abdominal pain, or fluid refusal within 7 days, not including scheduled visits (e.g. reassessments, vaccinations), will also be measured using follow up questionnaires 24, 48, and 168 hours (7 days) after Time 0. Questionnaires will ask caregivers if they brought their child to a health care provider for an unscheduled visit related to the current illness. If a return visit occurred, further questions will be asked related to **Intravenous (IV) insertion**, treatment course, and disposition. Return to care data will be confirmed by reviewing the participant's hospital chart, where

possible. This outcome is important as > 50% of children have a follow-up office visit, 8-18% require an ED visit, and 5-8% are hospitalized.

A **5-point Likert scale will be used to determine caregiver satisfaction** with the therapy provided (ondansetron or placebo oral solution) in the 48 hours following Enrollment in the study.

The following **secondary safety endpoints** are important as they will add more information about the secondary objective. The safety endpoints will include:

- 1) Serious Adverse Events (SAEs)
- 2) Frequency of diarrheal episodes during the 48-hours following ED disposition
- 3) Maximal number of diarrheal episodes in 24 hours
- 4) Palpitations
- 5) Pre-syncope/syncope
- 6) Chest Pain
- 7) Arrhythmias

All safety end point data will be obtained via participant follow-up questionnaires performed 24, 48, and 168 hours (7 days) after enrollment (Time 0). **Frequency and maximal number of diarrheal episodes** will be obtained by asking about presence of diarrhea on each questionnaire the caregiver completes. If diarrhea is present, further questions related to number of episodes will be asked. To obtain SAE and palpitation data, each questionnaire will contain open ended, non-symptom specific questions where caregivers can provide the study team with information about their child's illness or any other concerns they may have. Any response provided to this question will result in a trained study team member discussing the information provided in more detail via telephone. Any symptom or condition noted that meets the definition of an SAE (see Section 8.3.2) will be reported as outlined in Section 8.3.6.

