## 4.4 END OF STUDY DEFINITION

The end of the study is defined as completion of the last visit or procedure shown in the SoA in the trial globally.

A participant is considered to have completed the study if they have completed all phases of the study including the Day 7 email or telephone questionnaire shown in the SoA in Section 1.3. Emergency Department chart review of enrollment/baseline data is performed by study staff at each site and does not involve direct participation by the study participant or caregiver.

It is not necessary for caregivers to administer all study medication doses provided to them to remain compliant with the protocol. Doses are administered based on caregiver assessment of the child's need. The number of

doses administered by the caregiver will be recorded on the follow-up questionnaires completed by email or telephone.

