- Frequency and duration of diarrhea
- Presence of fever
- Return to healthcare provider (resource utilization)
- IV rehydration
- Satisfaction with care and medications provided

**Chart Review:** The study consent form will contain details regarding the review of medical charts for study purposes. At the baseline/enrollment visit, the ED medical record will be reviewed to collect data points outlined on the Enrollment CRF including, but not limited to; triage date/time, ED disposition, discharge date/time, triage weight, triage temperature, and medications administered during the ED enrollment visit.

A review of the participant's medical chart will also take place between 8 – 30 days after the 168 hour time-point to collect data related to revisits to a health care provider that occurred within 7 days of enrollment for the current illness as defined in Section 3.0. Information regarding type of revisit, treatment provided, discharge diagnoses, and disposition will be collected.

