#### 9.4.4 SAFETY ANALYSES

**Secondary safety outcomes** will be obtained via participant follow-up questionnaires performed 24, 48, and 168 hours (7 days) after enrollment (Time 0 – consent date and time).

Summaries of incidence rates (frequencies and percentages), intensity, and relationship to study of individual AEs by System Organ Class and Preferred Term (MedDRA) will be prepared. All AEs beginning after randomization but before discharge will be included. Basic summaries by assigned groups will be prepared. The DSMB may request to see more detailed tables. The occurrence of any adverse event will be considered as a dichotomous outcome.

To obtain SAE, palpitation, pre-syncope/syncope, chest pain, and arrhythmia data; each questionnaire will contain open ended, non-symptom specific questions where caregivers can provide the study team with information about their child's illness or any other concern they may have. Any response to this question will result in a trained study team member discussing the information provided in more detail via telephone. Any symptom or condition that meets the definition of an SAE will be categorized as such and reported appropriately.

1. **Frequency of diarrheal episodes during the 48-hours following ED disposition:** Frequency and maximal number of diarrheal episodes will be obtained by asked about presence of diarrhea on each questionnaire the caregiver completes. If diarrhea is present, further questions related to the number of episodes will be asked. Frequency will be calculated over 48 hours for all patients regardless of whether they have greater than 24 hours with no symptoms.
2. **Maximal number of diarrheal episodes in 24 hours:** Same as above – Frequency
3. **Serious Adverse Events (SAEs)**
4. **Palpitations**
5. **Pre-syncope /syncope**
6. **Chest Pain**

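### The plan gives incompatible adverse event windows: onsets are to be recorded past the last scheduled contact, and the safety tables carry a third, unclear cut-off

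*Combined protocol and SAP*

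**What the plan says.** - **Recording window.** Section 8.3.4 has staff record reportable events with onset from consent "until 7 (for non-serious AEs) or 15 days (for SAEs) after the last day of study participation".
- **Scheduled contacts.** The same section says "Adverse Events will be assessed via telephone or email contact with the caregiver 24, 48, and 168 hours after enrollment in the study". Each contact asks about events since the previous one, and the date and time of onset are collected. Events may also surface "if a study participant presents for medical care to the enrolling ED, or upon review of data by a study monitor".
- **Safety endpoints.** Section 3 states "All safety end point data will be obtained via participant follow-up questionnaires performed 24, 48, and 168 hours (7 days) after enrollment". Section 9.4.4 likewise says that the secondary safety outcomes "will be obtained via participant follow-up questionnaires performed 24, 48, and 168 hours (7 days) after enrollment".
- **End of participation.** Section 1.3 states "The study period will last 168 hours (7 days) from the Screening/Enrollment Visit to the Final Evaluation". Section 4.4 counts a child as having completed once all phases are done, "including the Day 7 email or telephone questionnaire shown in the SoA". Section 1.3 also gives the questionnaires 14 extra days, and its footnote treats a contact as out of window only after 21 days from randomization.
- **Chart review.** Section 8.1 places it 8 to 30 days after the 168-hour point and limits it to "revisits to a health care provider that occurred within 7 days of enrollment for the current illness".
- **Table rule.** For the adverse event summaries, section 9.4.4 takes in events that begin after randomization and before discharge. It does not say which discharge.
- **Schedule table.** The adverse event review row in section 1.3 is marked at baseline and at 168 hours only. Sections 8.2 and 8.3.4 put adverse event assessment at 24, 48 and 168 hours, and 8.3.4 cites section 1.3 for this.

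**The concern.** Three end points compete. Section 8.3.4 records onsets well past Day 7. The solicited contacts stop at the last questionnaire, whenever it is completed. The table rule in section 9.4.4 stops at discharge. An analyst working from this text cannot tell which events belong in the by-arm adverse event and serious adverse event tables.

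Two things are at stake. A serious event count described as covering the period to Day 22 would mix a solicited first week with a later period in which nobody was asked. And if discharge means discharge from the ED, the summaries would omit the period in which the study drug is taken, since dosing happens at home.

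**Working it through.** **Inputs.** Last questionnaire at 168 hours; completion allowance 14 days (section 1.3); recording extension 7 days for non-serious and 15 days for serious events (section 8.3.4). Consent, randomization and enrollment all fall in the index ED visit, so all are treated as Day 0.

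**The plan's own limits first.** 168 / 24 = 7 days. 7 + 14 = 21 days, which agrees with the footnote in section 1.3. 7 + 30 = 37 days, which agrees with the chart review limit in section 9.4.2.

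**Share of the recording window with no solicited contact.** Share = (window end − last contact) / window end.

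| Reading of the last day of participation | Last contact | Non-serious events | Serious events |
|---|---|---|---|
| Day 7 | Day 7 | (14 − 7)/14 = 50% | (22 − 7)/22 = 68% |
| Day 7 | Day 14 | 0% | (22 − 14)/22 = 36% |
| Day 7 | Day 21 | 0% | (22 − 21)/22 = 5% |
| Moves to the late contact | Day 21 | (28 − 21)/28 = 25% | (36 − 21)/36 = 42% |

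In the last row the windows end at 21 + 7 = Day 28 and 21 + 15 = Day 36. The plan does not say whether the last day is fixed at Day 7 or moves with a late questionnaire, so both readings are shown.

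**Range of solicited follow-up.** It ends between Day 7 and Day 21, and 21/7 = 3. This range comes from the 14-day allowance together with the recall wording. The 7- and 15-day extension does not cause it. The documents give no share of late responders, so 3-fold is a limit and not a typical value.

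**Does the chart review close the gap?** It is performed from 7 + 8 = Day 15 to 7 + 30 = Day 37, but it looks back only at revisits for the current illness in the first 7 days. Sections 8.3.2 and 8.3.5 also keep hospitalization for gastroenteritis symptoms out of serious event reporting. The review therefore does not cover Days 8 to 22, and much of what it finds would not count as a serious event.

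**Is Day 7 late enough for drug effects?** Section 1.3 plans the final dose within 48 hours of the first clinical dose and treats dosing after 72 hours as a deviation. Section 6.2.2 gives a half-life of 3 to 4 hours after 8 mg. Taking five half-lives (15 to 20 hours) as washout is my assumption, and I ignore the difference between the clinical-dose clock and the consent clock.

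- Last dose at 48 h: washout by 63 to 68 h, leaving 168 − 68 = 100 to 168 − 63 = 105 h of observation.
- Last dose at 72 h: washout by 87 to 92 h, leaving 168 − 92 = 76 to 168 − 87 = 81 h.

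A window that ends at 168 hours therefore covers planned dosing and at least three further days.

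**The case against.** The strongest reply is that section 8.3.4 sets a duty to record and does not promise to ask. A passive tail after the last contact is a legitimate design, and the section itself names two passive routes: care at the enrolling ED and monitor review. A reader might infer that all adverse event data come from the questionnaires. That is accurate for the safety endpoints in section 3 but not for adverse events in general. A reader might also infer that both windows are mostly unobserved. On the nominal schedule the non-serious window is exactly half unsolicited, only the serious window is more than half, and both shares fall when the last contact is late.

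It can also be said that little inference depends on this. Serious events, palpitations, syncope, chest pain and arrhythmias are reported without formal testing, and diarrhea frequency has its own fixed 48-hour period. The procedures are the same in both blinded arms, and onset dates allow a cut-off to be applied at analysis.

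All of this stands, and it limits the point to one of interpretability. It does not answer the point. The plan nowhere says that the tail is passive, does not fix the last day of participation, and sets no usable common onset cut-off for the tables. The only cut-off it states, at discharge, conflicts with the rest. The mismatch in the schedule table is close to clerical, because the questionnaire row is marked at all three times.

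**Conclusion.** The concern holds as an inconsistency in the safety windows. On the nominal schedule, 7 of 14 days for non-serious events and 15 of 22 days for serious events rest on passive detection: the enrolling ED, monitor review or spontaneous report. As a separate matter, solicited follow-up ends anywhere from Day 7 to Day 21. The discharge rule in section 9.4.4 is the most consequential of the three if it means ED discharge; the text does not settle that.

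The figures assume that the last day of participation is Day 7 and that the contact is on time; the working shows how they change otherwise.

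A reader might go further and infer a bias between arms, or a serious event count that is falsely low. The documents do not support either. Nothing suggests that lateness differs by arm, no serious event rate is given, and Day 7 lies past planned dosing and washout. What is affected is the meaning of the descriptive rates. The change should be made, but the primary analysis does not depend on it.

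**What to change.** - **Section 9.4.4:** replace the discharge rule with one fixed onset window for the by-arm adverse event and serious adverse event tables: consent to 168 hours, by recorded onset date, however late the questionnaire is completed. List events with later onset separately, labelled as passively or spontaneously reported. Later events first mentioned in a late questionnaire also belong in this list, marked as such.
- **Section 8.3.4:** define the last day of participation, and state that events after the last contact are recorded only if they come to the site's attention.
- **Section 1.3:** reconcile the adverse event review row with sections 8.2 and 8.3.4.

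The cost is wording only, because onset date and time are already collected. A fixed window does not add observation for children who withdraw or are lost before 168 hours.

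Extending the chart review to admissions and deaths through Day 22 is optional and not needed here. It would widen the scope of the review, and reviews done on Days 15 to 21 would have to be delayed or repeated. Care recorded elsewhere would still be missed, since section 9.4.3 accepts that records are incomplete.
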